## Background

Chronical obstructive pulmonary disease (COPD) is characterized by persistent and progressive airflow limitation associated with a chronic inflammatory response in the airways and lung parenchyma to noxious particles or gases [1]. COPD is a major cause of morbidity and mortality worldwide and its prevalence is expected to increase over the next decade because of continuous exposure to risk factors and the aging of the population [2]. It is estimated that in 2030 COPD will be the fourth leading cause of death globally [3]. Currently, the prevalence of the disease in Spain is 10.2% of the population between 40 and 80 years of age [4].

Dyspnoea, along with chronic cough and sputum production, is one of the main symptoms of COPD. Its severity and magnitude increase as the disease progresses and this disease is the main cause of disability and reduced quality of life in patients with COPD [5].

Patients may experience periods of acute exacerbation of COPD (AECOPD), defined as “a sustained worsening of the patient’s condition, from the stable state and beyond normal day-to-day variations, which is acute in onset and necessitates a change in regular medication in a patient with underlying COPD” [6]. These can be particularly severe exacerbations requiring hospitalization. In Spain, it is estimated that hospitalizations for AECOPD have an average cost of 344.96 euros per person per day [7], most of which is due to stays in hospital. These exacerbations are associated with 12% of mortality and 35% of readmissions up to 3 months after discharge [8].

Treatment of AECOPD includes bronchodilators, corticosteroids, antibiotics, oxygen therapy and non-invasive mechanical ventilation [9]. In the case of severe dyspnoea, oral or parenteral administration of opioids is recommended, although these have side effects and can cause respiratory depression [5]. However, dyspnoea remains a major symptom in patients hospitalized for an AECOPD [7].

The acupoint transcutaneous electrical nerve stimulation (AcuTENS) is a modern technique based on traditional acupuncture. It involves the stimulation of acupuncture points by using transcutaneous electrical nerve stimulation (TENS) instead of needles, which makes it a very-easy-to-learn, non-invasive method without the traditional acupuncture adverse effects such as infections or puncture of internal organs [10].

Several clinical studies using AcuTENS in patients with COPD have recently been published. All studies have used the stimulation of the acupuncture point named Dingchuan (EX-B1), traditionally used to treat dyspnoea. In those studies, a decrease in dyspnoea and an increase in forced expiratory volume in 1 second (FEV 1), β-endorphin level and quality of life have been observed [11–13]. However, these studies have been conducted on patients in stable condition, and little is known about the possible effect of this technique in patients with an AECOPD. Only one case study suggesting possible benefits for shortness of breath besides an increase in the level of oxygen saturation and β-endorphins has been published to date [14], and properly designed randomized placebo-controlled trials are needed to confirm these results.

The objectives of this study are to determine whether the use of AcuTENS at the Dingchuan point (EX-B1) could be beneficial for patients hospitalized for AECOPD by reducing dyspnoea, days of hospitalization, and consumption of regular medication. Moreover, we will assess possible adverse effects of this technique and its effect on mortality and readmissions at 3 months after discharge.

## Trial design

This is a multicentre, randomized controlled trial with blinded patients and assessors with a 1:1 allocation and two parallel groups. Trial registration dataset and SPIRIT 2013 checklist are available in Additional files 1 and 2.

## Methods

### Study setting

The study will be performed at the “Hospital del Mar” in Barcelona (Spain) and the “Hospital de Sant Joan de Déu de Manresa” in Manresa (Spain).

### Participants

The study subjects will be patients admitted at the study centres for an AECOPD. Participants will be recruited at the time of their admission by the pulmonology service and hospital emergency staff by using the following inclusion criteria: (1) patients between 45 and 75 years of age with a diagnosis of COPD in accordance with Global Initiative for Chronic Obstructive Lung Disease (GOLD) guidelines, (2) patients with one episode of hospitalization for COPD exacerbation in the past year but not more than three episodes, (3) smoking habit history of more than 10 packs a year, (4) patients able to correctly understand and answer the modified Borg scale, (5) patients with an initial degree of dyspnoea with a score of at least 5 in the modified Borg scale at recruitment, (6) patients recruited for the study during the first 48 h of hospitalization, and (7) patients who agree to participate in the study and sign the informed consent form.

Exclusion criteria will be (1) patients with any contraindication for transcutaneous electrical stimulation (patients with pacemakers, skin injury in the application area, etc.) and (2) patients with any cardiovascular, neurological or psychiatric disease that may affect the perception of dyspnoea.

### Interventions

In both groups, the Dingchuan point (EX-B1) will be localized bilaterally at 0.5 “cun” from the midline between the posterior spinous processes of C7 and T1 (Fig. 1). Afterwards, a conductive plastic sheet between the skin and the electrodes will be placed. These sheets have a hole of about 0.5 cm in diameter, which will coincide with the point above. Finally, the electrodes will be fixed with tape.

In the AcuTENS group (experimental), the stimulation is performed by using a portable TENS electrostimulation device (Sale & Service TN23) that uses a biphasic rectangular wave with a frequency of 2 Hz and a pulse width of 200 mS. The stimulation will be achieved by using the highest intensity tolerated by the patient without pain.

**Fig. 1 Fig1:**
[figure not shown]
Location of Dingchuan acupuncture point

The TENS simulated group (control) will have electrostimulators that are the same make and model as the experimental group but that have been modified to have no electrical outlet, even though the screen will light up and display the same data as in the unmodified device. Patients in this group will be informed that, owing to the frequency of stimulation, it is unlikely they will feel the electric stimulation.

In both groups, the session will last 45 min and will take place during a maximum of five consecutive days or until the patient is discharged.

If the acuTENS stimulation produces any kind of discomfort, the intensity of the current being applied to the patient will be reduced. If for any reason a treatment cannot be administered or is administered differently from the original protocol (e.g., only 30 min of treatment because the electrostimulation device had no battery), this will be reported. Any discomfort or skin reaction will be reported as an adverse event.

The interventions will be performed by physiotherapists or physicians who have a minimum of one year of clinical experience and who have been trained in the handling of the two treatment protocols. There will be a pre-pilot test to detect potential problems and ensure the adequacy of the implementation of the protocols.

Adherence to the treatment will be reported. No special stages for improving adherence will be taken since all patients will be hospitalized in the participating centres.

Both groups will receive the standard treatment for patients with AECOPD (bronchodilators, steroids, etc.) in accordance with medical criteria as well as the treatment with acuTENS or simulated acuTENS. No treatment is prohibited.

### Outcomes

#### Primary outcome measure

The primary outcome of this trial will be dyspnoea using the modified Borg scale. Evaluators will show a printed Borg scale to patients and explain the meaning of each punctuation and then patients will be asked to rate their dyspnoea. Data will be assessed at baseline and after each treatment session (days 1 to 5). Differences will be assessed by comparing groups’ mean scores at each day (days 1 to 5). The modified Borg scale is a valid and reliable assessment tool for dyspnoea in patients with an AECOPD [15].

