### Sample size

Considering a minimal clinically important difference regarding dyspnoea, measured by the Borg scale, of 2 [16] and assuming a common standard deviation of 2.6, an α error of 0.05, a β error of 0.2 and a 10% rate of losses, we calculate that we will need to recruit 60 patients for this study. To reach this target sample size, pulmonology service and hospital emergency staff will be informed so they can detect possible candidates.

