### Statistical methods

There will be a descriptive analysis of the demographic data by using means and standard deviations (mean ± standard deviation) for continuous variables and absolute values and percentages for qualitative outcomes.

For the comparative analysis between the two groups, continuous outcomes (such as Borg scale score and number of hospitalization days) will be analysed by using mean differences with a 95% confidence interval with a Student *t* test or Mann–Whitney *U* test depending on the distribution of these. For dichotomous outcomes (such as mortality at 3 months), risk ratio will also be used with a confidence interval of 95% and chi-squared test.

The main analysis will be carried out by intention to treat, but there will be another per-protocol analysis for patients who have received at least three interventions. A *P* value of less than 0.05 will be considered significantly different.

In case of missing data, last value carried forward methods will be used. In case of significant baseline differences between the two groups, there will be an adjusted analysis for these outcomes.

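### The primary outcome is compared on five separate days at an unadjusted 0.05, while the 60 patients are sized for one comparison; the protocol does not say which result would make the trial positive

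*Protocol article*

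**What the plan says.** Three places in the protocol article bear on this.

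- **Primary outcome measure.** Borg dyspnoea is collected repeatedly: "Data will be assessed at baseline and after each treatment session (days 1 to 5"). The comparison is then fixed: "Differences will be assessed by comparing groups’ mean scores at each day (days 1 to 5"). No day is singled out, and no average, overall test or ordering of the days is given.
- **Statistical methods.** Continuous outcomes, with the Borg score named as an example, "will be analysed by using mean differences with a 95% confidence interval with a Student" t test, or with a Mann–Whitney test, depending on distribution. One threshold covers everything: a P "value of less than 0.05 will be considered significantly different". No adjustment for several tests is mentioned, and missing values are filled by carrying the last one forward.
- **Sample size.** The inputs are one difference ("Considering a minimal clinically important difference regarding dyspnoea, measured by the Borg scale, of 2"), one SD ("assuming a common standard deviation of 2.6"), "an α error of 0.05", a beta of 0.2 and 10% losses. The result is "we calculate that we will need to recruit 60 patients for this study". No day is attached to the difference or the SD.

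**The concern.** The outcome section describes five between-group tests of the primary outcome; the sample size section describes one. An alpha of 0.05 and a power of 80% belong to a single test, and the text does not say which of the five it is, or how five P values combine into one conclusion.

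This matters because the choice decides whether the trial is called positive. If it is left open until the results are seen, a reader cannot tell a planned finding from the most favourable of five days. The two obvious ways of combining the days pull in opposite directions: one raises the false-positive risk above 5%, and the other takes the power below 80%.

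**Working it through.** **Inputs from the protocol.** Difference 2, SD 2.6, alpha 0.05, power 0.80, losses 10%, 1:1 allocation, total 60, five daily comparisons. Two-sidedness is inferred from the 95% confidence intervals.

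**Assumed, because the protocol gives no value.** The within-patient correlation between days, taken as 0.5 to 0.9 with 0.3 and 0.95 as extremes, either equal for all pairs of days or decaying with distance (AR(1)).

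1. **Reproduce the 60.** n per arm = 2 × SD² × (z₀.₉₇₅ + z₀.₈₀)² / difference² = 2 × 6.76 × (1.960 + 0.842)² / 4 = 26.5, rounded up to 27. Total 54, and 54 / 0.9 = 60, an exact match. A one-sided test would give 42, then 47 after losses. So the 60 is one two-sided test at 0.05.

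2. **False-positive risk if any one day suffices.** With independent days it would be 1 − 0.95⁵ = 22.6%, a ceiling for this purpose because a patient's daily scores are correlated. Simulating five correlated two-sample t tests with 27 per arm and no effect (100,000 runs) gives the chance of at least one P<0.05:

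| Assumed correlation | Equal correlation | AR(1) |
|---|---|---|
| 0.3 | 21.0% | 21.8% |
| 0.5 | 18.7% | 20.2% |
| 0.7 | 15.2% | 17.3% |
| 0.8 | 12.8% | 15.1% |
| 0.9 | 10.4% | 12.1% |
| 0.95 | 8.5% | 9.9% |

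   A separate simulation of correlated z statistics gives the same to within about a percentage point (18–20% at 0.5, 15–17% at 0.7, 10–12% at 0.9).

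3. **Effect of carrying values forward.** If 10–20% of the remaining patients are assumed to leave before each of days 3 to 5 and their last score is carried forward, the risk runs from 19.8% at correlation 0.3 down to 9.8% at 0.9. This is slightly lower, because later days partly copy earlier ones, but the inflation remains.

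4. **If all five days must be significant.** In the runs of step 2 the false-positive risk is at most 1.6% for correlations up to 0.9, and 2.4% at 0.95. Power cannot exceed that of one day, which is 79% with 27 per arm (exact t). Adding a true difference of 2 on every day to the simulation gives power of about 43% to 68% for correlations of 0.5 to 0.9.

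5. **If each day were tested at 0.05 / 5 = 0.01 (Bonferroni).** The noncentrality is 2 / (2.6 × √(2/27)) = 2 / 0.708 = 2.83 on 52 degrees of freedom. Power on a given day is 79% at 0.05 and 56% at 0.01. Restoring about 80% on a given day takes 40 per arm by the formula in step 1, and 80 / 0.9 = 89 patients, or 90 for equal arms. The power to detect an effect on at least one day is a different quantity: about 71% to 93% for correlations of 0.9 to 0.5, if the difference of 2 is present on all five days.

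6. **Whether the 60 fits a five-day average.** If 2.6 is the SD of a single day's score, the SD of the five-day mean under equal correlation r is 2.6 × √((1 + 4r)/5): 2.01 at r = 0.5 and 2.27 at r = 0.7. The averaged difference need not be 2 either. The stated calculation does not describe that contrast.

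**The case against.** - **No any-day rule is written.** This is the strongest objection, and it stands. A reader might infer that the trial's false-positive risk is two to four times 5% as a matter of fact. The protocol does not support that: it gives no criterion for a positive trial, and an all-days rule would put the error below 5%. The inflation is conditional.
- **The correlation is unknown.** This also stands. At 0.95 the factor is only about 1.7 to 2.0, and at 0.3 it exceeds four. Carrying values forward lowers it slightly.
- **A later correction need not destroy the power.** A reader might infer from the fall from 79% to 56% that a Bonferroni-corrected trial would have 56% power. That figure is for one given day. The power to find an effect on at least one day could be at or above 80% when the between-day correlation is about 0.7 or lower and the effect is present throughout.
- **The article is condensed, and an analysis plan may name a day or an adjustment.** This is fair as far as silence goes. But the article is not silent: under the primary outcome it states a comparison at every day, with a single significance threshold. An analysis plan naming one contrast would alter that stated analysis, so the text needs reconciling either way.
- **The daily tests may be meant as descriptive.** They are the only analysis given for the primary outcome, and a significance threshold applies to them.

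**Conclusion.** The point holds in a conditional form. The primary analysis as written (five daily tests at 0.05) and the sample size (one two-sided test at 0.05) do not describe the same comparison, and no success rule connects them.

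If any one significant day were taken as success, the false-positive risk would be about 10–12%, 15–17% or 18–20% at assumed between-day correlations of 0.9, 0.7 or 0.5. If all five were required, it would be below 5%, but the 80% power would not apply. Only one prespecified test keeps the stated alpha, and the stated power goes with it only if the difference of 2 and the SD of 2.6 are those of that test. The mismatch rests on the text and an exact reproduction of the 60; the percentages rest on the assumed correlation and the assumed decision rule.

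**What to change.** Before unblinding, name one primary contrast, test it once at 0.05, and report the other daily differences with 95% confidence intervals as secondary. There are two workable forms:

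- **The Borg difference at one named day.** The 60-patient calculation stands as it is; add that the difference of 2 and the SD of 2.6 refer to that day.
- **The day 1–5 average from a single repeated-measures model.** Restate the SD, the difference and the power for that average rather than attributing the present calculation to it. Also say how scores after discharge are handled in place of last value carried forward.

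The first form costs only wording. The second also needs a fresh calculation and a missing-data rule. Neither calls for extra assessments. The price in both cases is that success can no longer be claimed on whichever day turns out significant.

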#### Secondary outcome measures

Hospitalization length will be measured by using the number of days from the time of admission until the patient’s discharge. Scores will be compared by using mean differences between groups.

Peak expiratory flow will be assessed by using a peak flow meter and using litre per minute units at baseline and after each treatment session. For each assessment, peak flow will be measured three times and only the highest score will be considered. Differences will be assessed between groups by using mean scores at each day (days 1 to 5).

Adverse events will be recorded after each treatment session; the evaluator will ask the patient for any adverse event related to the intervention. Description of each event and its frequency will be described for each group.

Blood gas analysis—partial pressure of oxygen (PaO_2_), partial pressure of carbon dioxide (PaCO_2_), arterial blood pH, bicarbonate and oxygen saturation (SaO_2_)—at days 1 to 5 will be recorded if available in the patient’s clinical history since no specific analysis will be made for the trial. Differences will be assessed by comparing means at each day (days 1 to 5).

Relapse and readmissions at 3 months after discharge will be assessed by using the participant’s clinical history. Mean number of relapses and readmissions during the 3-month period after discharge will be compared between groups.

Mortality will be assessed by using the ratio of patients who died during the 3-month period after discharge in each group.

Quantity of drugs administered during patient’s hospitalization will be extracted from the patient’s clinical history. Mean dosages will be compared between groups. Data will be collected by using a standard form designed by the study investigators, and database entry will be double-checked.

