### Blinding

Trial participants, outcome assessors and usual care providers will be blinded during the trial, and only the physiotherapists who will perform the acuTENS or sham acuTENS procedure will know the patient’s allocation. To ensure that they remain blinded to allocation, the medical staff will not be present during the application of technology. There will be no circumstances under which unblinding is permissible. Data analysis will be performed by a blinded external statistician.

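### Having the evaluator ask about intervention-related adverse events after each session puts the blinding of later Borg and peak-flow ratings at risk, to an unknown extent

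*Protocol article*

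**What the plan says.** Five statements in the Protocol article bear on this point.

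- **Primary outcome measure.** "Evaluators will show a printed Borg scale to patients and explain the meaning of each punctuation"; the patient then gives the rating. Ratings are taken at baseline and after every session, on days 1 to 5. Peak flow follows the same timetable (Secondary outcome measures), though the article does not name who takes it.
- **Secondary outcome measures.** "Adverse events will be recorded after each treatment session; the evaluator will ask the patient for any adverse event related to the intervention".
- **Blinding.** "Trial participants, outcome assessors and usual care providers will be blinded during the trial". Only those giving the procedure are to know the allocation, and medical staff stay away while the device is applied.
- **Interventions, active arm.** "The stimulation will be achieved by using the highest intensity tolerated by the patient without pain".
- **Interventions, sham arm.** The device is "modified to have no electrical outlet, even though the screen will light up and display the same data as in the unmodified device". Sham patients are told they will probably not feel the stimulation.

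The Interventions section also counts discomfort and skin reactions as adverse events, and it limits treatment to five daily sessions, ended earlier by discharge.

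**The concern.** The article uses the same role word for the person who presents the Borg scale and the person who asks about events related to the intervention. Both tasks fall at the same time point, after each session, and no separate collector of adverse events is named. The question concerns the very thing that differs between the arms. Current flows in one arm only, so an answer that attributes discomfort to the current points to the active arm. A sham patient might likewise repeat having been told to expect no feeling.

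An evaluator who has heard such an answer returns the next day to explain the Borg scale and take the rating. Peak flow, kept as the highest of three attempts, is also open to the influence of whoever takes it. The stated safeguard does not help, because it applies during stimulation and the question comes afterwards. What is at stake is the claim of blinded assessment for the primary outcome and for peak flow.

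**Working it through.** **The plan's own figure.** The only design figure is the sample size. The inputs are a difference of 2, SD 2.6, α 0.05 (sidedness not stated; two-sided taken), power 0.80 and 10% losses. With the normal approximation, n per arm = 2 × (1.960 + 0.842)² × 2.6² / 2² = 2 × 7.85 × 1.69 = 26.5, rounded up to 27. Then 27 / 0.90 = 30 per arm, 60 in total, as stated. Nothing below changes it.

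**Ratings exposed to an earlier question.** A patient with m sessions has m post-session ratings, of which m − 1 follow a question put at an earlier session.

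- m = 5: 4 of 5 (80%)
- m = 3: 2 of 3 (67%)
- m = 1: 0 of 1

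The article does not give the order of rating and question within a visit. This count therefore takes the rating first each day, which protects that day's rating but not later ones. It counts ratings that come after a question, not ratings taken unblinded.

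**Ratings that follow a revealing answer.** This needs the chance p that an active patient gives a revealing answer at a session. The article has no such figure and none can be derived from it, so p is an assumption and a wide range is shown. The table further assumes five sessions for everyone, independence between sessions, the same evaluator throughout, and revealing answers in the active arm only.

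- Revealed by the end of session k: 1 − (1 − p)^k
- Share of the five active-arm ratings taken after an earlier revealing answer: the mean of 1 − (1 − p)^(k−1) over k = 1 to 5
- Share of ratings in both arms: half of that, with 1:1 allocation

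| p (assumed) | Revealed by session 1 | Revealed by session 5 | Active-arm ratings affected | Ratings affected, both arms |
|---|---|---|---|---|
| 0.05 | 5% | 23% | 9.5% | 5% |
| 0.10 | 10% | 41% | 18% | 9% |
| 0.30 | 30% | 83% | 45% | 22% |
| 0.50 | 50% | 97% | 61% | 31% |

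Worked case, p = 0.10: (0 + 0.100 + 0.190 + 0.271 + 0.344) / 5 = 0.181.

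The table shows how a per-session question accumulates. It is not an estimate for this trial. Revealing every active patient at session 1 requires p = 1.

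**The case against.** A reader might infer that assessor blinding is lost from day 1, or that the schedule itself breaks it. The documents do not support that, for these reasons.

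- **The question is not the leak.** It applies to both arms, and only an arm-specific answer reveals anything.
- **The event asked about may be uncommon.** The intensity is set short of pain, and the current is reduced if it causes discomfort. The enquiry is about adverse events, not about every sensation.
- **Answers are not cleanly diagnostic.** Both arms have the conductive sheet, electrodes and tape, so a sham patient can also report a skin reaction. An answer of no event identifies neither arm.
- **One person doing both tasks is an inference.** The shared role word makes it the natural reading, but the article does not say that the same individual does both for a given patient. Task order and division of roles are details an article may leave to the full protocol, and the schedule figure is not available.
- **The Borg score is the patient's own.** An evaluator's knowledge can act only through how the scale is presented or recorded.

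All of this stands as a limit on size and certainty. It also rules out a headcount of unblinded patients, which would need an event rate the article does not give. What remains does not depend on missing detail. The article assigns the question to the evaluator, repeats it before later ratings, and states a safeguard that does not reach it.

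There is also a fair argument for the present arrangement. Adverse effects are a stated objective, and a blinded person eliciting them is a defensible choice. That argument bears on which remedy to choose.

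**Conclusion.** The point holds as a risk to assessor blinding, not as a demonstrated loss of it. Read as written, the Secondary outcome measures section opens a route by which the evaluator can learn the arm before later Borg and peak-flow ratings, and this sits badly with the Blinding section. Up to 4 of 5 post-session ratings come after a question from an earlier session, and fewer in patients discharged early. The number actually compromised cannot be quantified from the documents.

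The conclusion rests on two readings: that evaluator means the same role in both outcome sections, and that those who take Borg and peak flow are among the assessors declared blinded. It is worth correcting because the correction is cheap. No sample-size figure is affected.

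**What to change.** Reword the adverse-event sentence in Secondary outcome measures so that the Borg and peak-flow evaluator no longer asks about adverse events.

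- At each visit the evaluator takes Borg and peak flow first and asks nothing about the device.
- The patient then completes a short adverse-event checklist, identically worded in both arms, which is kept sealed from the evaluator. Alternatively, the treating therapist administers the same checklist.
- Patients are asked not to describe device sensations to the evaluator.

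Changing the order alone would not be enough, since it protects only the same day's rating.

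The cost is a change of wording and one form, with no extra staff or visit. The drawback lies in the alternative: if the treating therapist administers the checklist, harms are elicited by someone who knows the arm, and fixed wording limits that bias without removing it. The self-completed form is therefore preferable, with the therapist as the fallback.

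### The adverse event question asks patients only about events related to the intervention, which is narrower than the rule under Interventions and can miss symptoms that patients blame on COPD

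*Protocol article*

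**What the plan says.** Assessing harm is a stated aim. The Background closes its objectives with "we will assess possible adverse effects of this technique and its effect on mortality and readmissions at 3 months after discharge".

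Two places in the protocol article fix how adverse events are collected:

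- **Secondary outcome measures.** Timing is general: "Adverse events will be recorded after each treatment session". The means of collection is then specified: "the evaluator will ask the patient for any adverse event related to the intervention". Reporting is descriptive: "Description of each event and its frequency will be described for each group".
- **Interventions.** A second rule carries no condition on cause: "Any discomfort or skin reaction will be reported as an adverse event".

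The Interventions section also describes what each arm experiences. For the active arm, "The stimulation will be achieved by using the highest intensity tolerated by the patient without pain". The control devices deliver no current, and "Patients in this group will be informed that, owing to the frequency of stimulation, it is unlikely they will feel the electric stimulation". No matching information for active patients is stated.

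**The concern.** The wording under Secondary outcome measures puts a causal judgement in front of recording and gives it to the patient. These patients are in hospital with an acute exacerbation and a Borg score of at least 5 at recruitment, so the disease is a ready explanation for almost any new symptom. A patient who holds that view will truthfully answer no, and the question yields nothing to record. Unexpected effects are the ones a patient is least likely to connect with a device on the neck. The Background itself says that little is known about the technique in exacerbations.

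A second possibility is that attribution differs by arm. An active patient may feel current and a sham patient has been told not to expect to, so the same symptom could be linked to the device more readily in the active arm.

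At stake is how complete the adverse event outcome is for the treatment days, and how far its counts by group can be read as a comparison.

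**Working it through.** **1. The two collection rules side by side**

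| | Secondary outcome measures | Interventions |
|---|---|---|
| Scope | Any type of event | Discomfort and skin reactions |
| Condition on cause | Must be related to the intervention | None |
| Who judges cause | The patient, when asked | Nobody |

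For discomfort and skin reactions the two rules disagree on whether relatedness is required. For every other kind of symptom, the conditional question is the only stated means of soliciting it.

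**2. What other outcomes capture without attribution**

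- Breathlessness: Borg score after every session (primary outcome).
- Airflow: peak flow after every session.
- Blood gases: days 1 to 5, but only if already in the clinical history.
- Relapse, readmission and death: no attribution needed, but counted over the 3 months after discharge, so not during the treatment days.

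What remains exposed is symptoms during the treatment days (at most five) that are neither discomfort nor skin reactions and do not show in the Borg score or peak flow.

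**3. Patients per arm**

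Inputs from Sample size: difference 2, SD 2.6, α 0.05 (two-sided assumed), β 0.2, losses 10%. Allocation is 1:1 (Trial design).

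n per arm = 2 × (1.960 + 0.842)² × 2.6² / 2² = 26.5, rounded up to 27. The total is 54, and 54 / 0.9 = 60. The plan's figure of 60 is reproduced, which gives 30 per arm.

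**4. Chance of recording no event in the active arm**

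Let p be the true proportion of patients with an event of the exposed kind and a the probability that the patient attributes it to the intervention. The documents give neither, so both are assumed. With independent patients and the question as the only route:

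P(no recorded event) = (1 − p × a)^30

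| p | a = 1 | a = 0.5 | a = 0.25 |
|---|---|---|---|
| 10% | 0.90^30 = 4% | 0.95^30 = 21% | 0.975^30 = 47% |
| 5% | 0.95^30 = 21% | 0.975^30 = 47% | 0.9875^30 = 69% |

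**5. Effect on the comparison between arms**

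With the same p in both arms, the recorded risk ratio is (p × a_active) / (p × a_sham) = a_active / a_sham. Expected counts below assume p = 0.40 and 30 per arm.

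| a_active v a_sham | Recorded risk ratio | Expected counts |
|---|---|---|
| 0.5 v 0.5 | 1.0 | 6.0 v 6.0 |
| 0.6 v 0.4 | 1.5 | 7.2 v 4.8 |
| 0.7 v 0.3 | 2.33 | 8.4 v 3.6 |

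With equal attribution, half the events are lost but the arms stay comparable. A distortion arises only if attribution differs, and in the direction suggested here it raises the active count relative to sham.

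**The case against.** The best defence has four parts.

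- **The collection is not limited to what patients attribute.** A reader might infer that an event counts only if the patient links it to the device. The documents do not support that: the Interventions rule has no such condition and covers the effects most expected from surface stimulation, and the sentence on recording after each session is itself unrestricted. This stands, and it limits the point to other kinds of symptom.
- **Respiratory worsening is measured anyway.** A reader might infer that worsening breathlessness would be lost. It would not, because it is the primary outcome and is scored after every session in both arms. This also stands.
- **Nothing says the arms will differ.** A reader might conclude that the arms are not comparable on safety. The documents do not show this. The control script concerns feeling the current, not other symptoms; patients and assessors are to be blinded; and one question is described for both arms. If attribution did differ as suggested, the device would look worse, so harm would not be hidden relative to sham. This stands as a limit on the claim. It does not remove the possibility, since a patient unaware of allocation can still link a symptom to a sensation.
- **It is a descriptive secondary outcome, and the data form is not shown.** A condensed article need not reproduce the form. That would answer an omission, but here the article states the question and its condition.

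**Conclusion.** The point holds in a limited form. The question under Secondary outcome measures leaves causation to the patient before recording, and it is narrower than the Interventions rule. Symptoms during the treatment days such as palpitations or poor sleep can be missed when the patient blames COPD.

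The size cannot be fixed from the documents. Under the assumptions in the working, halving capture raises the chance of an empty active-arm record from 4% to 21% at a true rate of 10%, and from 21% to 47% at 5%. Those figures describe one arm and say nothing about comparability. Differential attribution is a plausible inference of unknown size.

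Three-month mortality and readmission, the primary analysis and the sample size are untouched. The change is worth making because assessing adverse effects is an objective and the remedy is cheap.

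**What to change.** Reconcile the two sections under one collection rule:

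1. After each session, ask both arms the same neutral, open question about any new or worsened symptom or event since the last contact, without mentioning the device.
2. Record every event whatever its presumed cause, including the discomfort and skin reactions already covered under Interventions.
3. Have study staff who are already blinded classify relatedness afterwards.
4. Report all events and related events separately by arm.

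The cost is a reworded question and a relatedness field on the data form, plus some staff time for classification. The small downside is more COPD-related events to record and code.
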